## Abstract

**Background:**

Since early 2022, patients with 2019 novel coronavirus (COVID-19) infection have increased rapidly in Shanghai, China. Nevertheless, there is no widely used unified rehabilitation treatment available for discharged patients with post-infection sequelae such as dyspnea, depression, and fatigue. To promote the rehabilitation of discharged patients, our team formulated Kangyi Qiangshen Gong exercise prescription on the basis of traditional Chinese medicine rehabilitation exercises (TCMRE). We designed a randomized controlled trial to evaluate the efficacy of rehabilitation and advantages of KQG for discharged patients with post-COVID-19 syndrome.

**Methods/design:**

This is a parallel-design, two-arm, analyst assessor-blinded, randomized controlled trial. In total, 60 discharged patients with COVID-19 sequelae, aged from 20 to 80 years will be recruited and randomly assigned to the World Health Organization instructed breathing techniques (BT) group and the Kangyi Qiangshen Gong exercise prescription (KQG) group at a ratio of 1:1. The patients in the BT group will perform breathing techniques exercise, and the patients in the KQG group will perform KQG exercise. Both groups will perform exercises twice a day for 3 months. The primary outcome will be measured with the Modified Medical Research Council Dyspnea Scale, and the secondary outcomes will include the Modified Borg Scale, Fatigue Scale-14, Patient Health Questionnaire-9 Scale, Pittsburgh Sleep Quality Index, and the Respiratory Symptoms Scale. Clinical scales will be assessed at three points (pre-exercise, 3 months post-exercise, and 3 months follow-up). Adverse events will be recorded for safety assessment.

**Discussion:**

This trial will serve high-quality evidence of the value of KQG for treating discharged patients with COVID-19 in rehabilitation period.

**Trial registration:**

Chinese Clinical Trial Registry ChiCTR2200059504. Registered on 03 May 2022.

**Dissemination:**

The results will be published in peer-reviewed journals and disseminated through the study’s website, and conferences.

## Background

COVID-19 epidemic is still expanding at a global level. Across the six World Health Organization (WHO) regions, over 7 million new cases and over 26,000 new deaths were reported. As of 12 April 2022, over 496 million confirmed cases and over 6 million deaths have been reported globally [1]. In March 2022, the number of patients with COVID-19 increased rapidly in Shanghai, China. As of April 12, 2022, 9903 patients had been diagnosed with COVID-19 infection in Shanghai, and 224,704 asymptomatic infections were still under medical observation [2]. With the continuous help of other provinces in China, the number of discharged COVID-19 patients in Shanghai gradually increased. The natural course of COVID-19 remains ill-defined, such as the frequency, nature, and duration of persistent symptoms, which presents the knowledge gap of the doctors [3]. Most previous studies have focused on hospitalized patients with COVID-19 rather than the sequelae of discharged patients. But it is reported that COVID-19 convalescent patients may leave sequelae, including dyspnea, fatigue, depression, sleep problems, or cognitive impairment (brain fog) [4–7]. Post-COVID-19 syndrome deteriorates the quality of life of discharged patients with COVID-19 [8, 9]. There is an urgent need to develop therapeutic strategies for effective rehabilitation of discharged COVID-19 convalescent patients [7, 10].

Prior studies [11–13] demonstrated that guidance on symptom management of COVID-19 patients in physical training had often been derived from clinical experiences and guidelines for the treatment of patients with other illnesses. Evidence on the efficacy and safety of palliative symptom control in COVID-19 patients remains lacking [13]. However, a recent study showed that exercises are beneficial to the rehabilitation of patients with post-COVID-19 syndrome by directly enhancing the respiratory muscle strength and the ability of pulmonary ventilation, inhibiting the storm of inflammatory cytokines, inhibiting intracellular and external oxidative stress, and regulating the intestinal flora [14]. Evidence suggests positive long-term effects of respiratory physiotherapy in post-acute COVID-19 adult patients [15].

Traditional Chinese exercise is a popular physical exercise in China. A systematic review showed that alternative medicine (CAM) like Qigong can significantly improve various psychological symptoms and physical symptoms in COVID-19 patients [16]. Previous studies [17] have shown that KQG is suitable for in-patients with mild or moderate COVID-19, which can significantly improve the physical quality of patients, enhance cardiopulmonary function, smooth emotions, and reduce fatigue. In China, only a rapid guide for exercise rehabilitation of discharged COVID-19 patients is provided, including traditional Chinese exercise rehabilitation methods such as Liu Zi Jue Qigong, Baduanjin Qigong, and Taijiquan [18–21]. Qigong is a traditional Chinese mind–body exercise and can improve sleep problems, fatigue symptom clusters, and depression [22–24]. In order to improve COVID-19 patients’ cardiopulmonary function, emotional disorder, and quality of life, we developed Kangyi Qiangshen Gong exercise prescription on the basis of previous researches [17, 25] and according to the application of multiple hospitals in Wuhan, China. KQG is a further optimized on the basis of Liuzijue Qigong, Baduanjin Qigong, Yijinjing Qigong, Wuqinxi, and Tai Chi.

However, there is still a lack of clinical evidence for its efficiency in the sequelae of discharged COVID-19 patients. We believe that KQG is also applicable to rehabilitation patients who meet the discharge criteria and can be used as an effective TCMRE therapy for family-centered intervention in the future. KQG has shown potential clinical effect on the various dimensions of COVID-19 which may improve patients’ quality of life, help them get back to work, and thus reduce the healthcare and economic burden on the society. This study can also provide evidence of evidence-based medicine on the KQG treatment of post-COVID-19 sequelae, which will contribute to the development of international expert consensus and play an important role in the prevention and treatment of the epidemic through traditional Chinese physiotherapy. Therefore, we designed a randomized controlled trial (RCT) to evaluate the rehabilitation efficacy and advantages of KQG in the treatment of discharged patients with post-COVID-19 sequelae. We hypothesize that Kangyi Qiangshen Gong exercise prescription will be more effective than breathing techniques in improving COVID-19 sequelae, which can be used as an effective TCMRE therapy for family-centered intervention in the future.

## Methods/design

### Study design

This will be a single-center, parallel-arm, superiority randomized controlled trial. A total of 60 patients will be recruited from the Shanghai Municipal Hospital of Traditional Chinese Medicine, Shanghai University of Traditional Chinese Medicine. All patients will be provided written informed consent at the time of recruitment. Patients with symptoms of dyspnea will be recruited and will have equal opportunity to be randomly assigned to either the BT group or KQG group. Only outcome assessors and statisticians will be blinded due to the limitations of the intervention methodology. Outcomes will be assessed and analyzed by the assessors at three time points (pre-intervention, 3 months post-intervention, and 3 months follow-up). Data management and statistics will be conducted at the School of Acupuncture-Moxibustion and Tuina, Shanghai University of Traditional Chinese Medicine (SUTCM). The flowchart in Fig. 1 illustrates the study design, and Fig. 2 shows the study schedule. Additional file 1 shows the Standard Protocol Items: Recommendations for Interventional Trials (SPIRIT) checklist.

**Fig. 1 Fig1:**
[figure not shown]
Flow chart of the trial. The present study is a randomized controlled trial. Sixty patients will be included and randomized equally to two groups, a BT group and a KQG group. For 30 patients in each group, this trial will include a 12-week treatment period. During the treatment, patients in the BT group will receive breathing techniques intervention, while the KQG group will receive KQG intervention. Both the outcome assessments will be performed at 3 time points, namely the baseline, the end of the treatments at 12 weeks, and 12 weeks of follow-up subsequently

**Fig. 2 Fig2:**
[figure not shown]
Study schedule showing the time points for enrollment and assessment. ADL, activities of daily living; CRF, case report form; CT, computed tomographic; mMRC, modified Medical Research Council; PHQ-9, Patient Health Questionnaire-9; PSQI: Pittsburgh Sleep Quality Index; RS, respiratory symptoms; TCMR, traditional Chinese medicine rehabilitation

### Participant recruitment

Patients recovered from COVID-19 formulated by post-COVID-19 symptoms will be recruited. In our study, subjects will be recruited from Shanghai Municipal Hospital of Traditional Chinese Medicine, Shanghai University of TCM. Recruitment methods included WeChat, online advertisements, posters, and leaflets. WeChat has currently been regarded as the most popular instant-messaging platform in China, with a large population base. Both the medical staff and patients have their own WeChat account, which make it easy and efficient to communicate online. Shanghai Municipal Hospital of Traditional Chinese Medicine is a tertiary hospital among the designated hospitals for the treatment of COVID-19 in Shanghai. Shanghai Municipal Hospital of Traditional Chinese Medicine has set up a specialized COVID-19 Rehabilitation Clinic for patients recovering from severe COVID-19 to provide TCM rehabilitation consultation, facilitating home rehabilitation through platforms such as internet hospitals, which could be a potential source of subjects. Formal screening process for participants will be conducted by the principal investigators (LF) or study coordinator (WC) to ensure the fulfillment of criteria below and informed consent form.

### Inclusion criteria

Patients with the following criteria will be recruited:

(1) discharged patients with COVID-19; (2) are male or female between the ages of 20 and 80; (3) have post-COVID-19 symptoms include but not limited to breath difficulties, fatigue, sleep difficulties, anxiety, or depression; (4) have a stable condition and remain conscious and cooperative during trial; (5) willing to join the trial and signed the informed consent form; (6) promise not to participate in other forms of exercise.

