#### Analysis of primary outcome

The primary outcomes will be evaluated at baseline, 12 weeks after the intervention, and follow-up. We will conduct sensitivity analyses for missing data (intention-to-treat analysis) and for adjustment of covariates of physical activity (adjusted intention-to-treat analysis). The primary endpoint is the mean change in mMRC Scales from baseline to the follow-up day. Baseline covariates included are sex, age category, history of cardiopulmonary disease, and body weight category. The whole outcomes scale will be measured at baseline. When normally distributed, the data will be analyzed with unpaired *t*-test for comparison between two groups, while for multiple comparisons one-way ANOVA and repeated measures (RM) ANOVA will be used. A sensitivity analysis using multiple imputation techniques (imputation using chained equations) will be included to assess the effect of missing data on the primary outcome. Besides, we will compare participants randomly allocated to BT group or KQG group, who received an allocated treatment that was deemed to be of high fidelity. The percentage of missing data is 20% and 5 imputed datasets will be used for analysis, which is the minimum recommended number. Prior to any analysis, any missing data pattern will be investigated and the reasons for missing data will be obtained and patterns will be investigated to judge the plausibility of missingness assumptions.

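### Entry sets no limit on time since discharge or on acute severity, and the fixed covariates omit both: a cost in precision, possible dilution and attribution, not bias in the randomised comparison

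*Protocol article*

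**What the plan says.** Under Inclusion criteria the index-illness and age conditions read "1) discharged patients with COVID-19; (2) are male or female between the ages of 20 and 80". The symptom condition is that patients "have post-COVID-19 symptoms include but not limited to breath difficulties, fatigue, sleep difficulties, anxiety, or depression". The nearest thing to a time or severity limit is that they "have a stable condition and remain conscious and cooperative during trial", which is not defined further. Study design adds that patients with dyspnoea will be recruited, again without a duration. Exclusion criteria set no interval and no severity class, but they do remove patients with conditions such as chronic obstructive pulmonary disease and coronary heart disease.

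Under Analysis of primary outcome: "The primary endpoint is the mean change in mMRC Scales from baseline to the follow-up day". Interventions gives 3 months of exercise and 3 months of follow-up, so the endpoint falls about 6 months after entry. The same analysis section fixes the covariates: "Baseline covariates included are sex, age category, history of cardiopulmonary disease, and body weight category". Randomization describes a random number generator and sealed envelopes and states no stratification factor.

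The Background concedes that "The natural course of COVID-19 remains ill-defined, such as the frequency, nature, and duration of persistent symptoms". Participant recruitment names as one possible source a "specialized COVID-19 Rehabilitation Clinic for patients recovering from severe COVID-19", alongside open advertising. The KQG experience cited in the Background is that "KQG is suitable for in-patients with mild or moderate COVID-19".

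**The concern.** The Abstract states the aim for post-COVID-19 syndrome, but entry requires only discharge and a symptom. A patient discharged the day before and one discharged in an earlier wave qualify on the same terms, as do patients after severe and after mild acute illness.

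The protocol's dates make recent cases likely. Shanghai's case numbers rose in March 2022, recruitment is planned for May 2022 and the trial is expected to end in December 2022. With about 6 months per patient, enrolment would have to close around the end of June.

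Three things are at stake. Patients who would recover anyway reach the floor of the mMRC scale in both arms and add nothing to the contrast at follow-up. Two plausible prognostic factors are neither balanced by design nor adjusted for, while one of the four covariate places goes to a history that the exclusions leave with little variation. And the result, positive or null, could not be assigned to persistent sequelae rather than to ordinary convalescence.

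**Working it through.** **Inputs.** Sample size calculation gives means of 0.74 (SD 0.55) for control and 1.52 (SD 0.54) for treatment, with 20% loss. The gap is 1.52 − 0.74 = 0.78. I use it as an absolute size only, because higher mMRC is worse and the stated direction favours control. Pooled SD = √[(0.55² + 0.54²)/2] = 0.545. Fig. 1 gives 30 per arm; 30 × 0.8 = 24 evaluable.

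**The plan's own figure.** For two means, two-sided 5%, 80% power: n = 2(1.96 + 0.84)² × (0.545/0.78)² ≈ 7.7, so 8 per arm, and 8/0.8 = 10 after loss (9 and 12 with the exact t). At 90% power it is 11 and 14 (exact t: 12 and 15). Neither the 60 per group stated there nor the 30 per arm stated elsewhere is reproduced. That is a separate defect; here it means only that the planned gap leaves a large margin of power.

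**Dilution.** Assume a share f recovers fully in both arms by follow-up and the SD stays at 0.545. The gap becomes 0.78 × (1 − f). The standard error with 24 per arm is 0.545 × √(2/24) = 0.157. Power from the noncentral t:

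| f (assumed) | Gap | Power, 24 per arm | Power, 48 per arm |
|---|---|---|---|
| 0 | 0.78 | 99.8% | above 99.9% |
| 25% | 0.585 | 95% | 99.9% |
| 40% | 0.468 | 83% | 99% |
| 50% | 0.39 | 68% | 93% |
| 60% | 0.312 | 49% | 79% |

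The last column applies if 60 per group are enrolled (60 × 0.8 = 48). With 24 per arm, 80% power needs a gap of about 0.44 (normal approximation), or 0.44/0.78 ≈ 57% of the planned one.

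**Chance imbalance.** With 30 per arm, the difference in means of a standardised factor has standard error √(2/30) = 0.258. It exceeds 0.25 SD with probability 33% and 0.5 SD with probability 5%. If the factor correlates r with mMRC change, the shift is imbalance × r × 0.545:

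- 0.25 SD: 0.04 grade at r = 0.3, 0.07 at r = 0.5.
- 0.5 SD: 0.08 grade at r = 0.3, 0.14 at r = 0.5.

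That is 5% to 17% of 0.78. The r values are assumptions.

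**Bias and precision.** Over 20,000 simulated trials with 24 per arm and an omitted baseline factor (r from 0 to 0.7), the mean error of the unadjusted contrast was about 0 and its type I error 4.9% to 5.1%. Adjusting for the factor reduced the standard error from 0.157 to 0.151 at r = 0.3 and to 0.137 at r = 0.5. At half the planned effect, power rose from 68% to 71% and 79% respectively.

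**The case against.** A reader might infer that spontaneous recovery confounds the KQG effect. The documents do not support that. Allocation is random and the control arm exercises on the same schedule, so recovery common to both arms cancels in expectation, and chance imbalance is already covered by the 5% level. This objection stands in full.

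A reader might also infer that the trial is underpowered. That too goes beyond the documents. No recovery rate is given, and power stays above 80% until roughly 40% of the planned gap is lost. The 0.78 comes from earlier KQG studies not shown here; if those patients were also recovering, discounting by f counts recovery twice. Some patients who have recovered by 6 months may still differ between arms at the 12-week assessment. The dilution figures are therefore a conditional range.

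The short calendar probably narrows the spread in time since discharge. That weakens the imbalance argument but strengthens the one about recovery.

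The protocol gives no duration definition of post-COVID-19 syndrome, and the Abstract's Discussion and the Background often describe the target simply as discharged or convalescent patients. So the entry rule does not break a stated definition. What stands is that the two descriptions sit side by side and support different conclusions.

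Finally, dates and severity may be on a case report form that a condensed article omits. That is fair, and their not being mentioned as recorded is not the point. The covariate list is stated, and it leaves both out.

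**Conclusion.** The point holds as one of precision, possible dilution and interpretation. The entry rule sets no interval and no severity criterion, and the fixed covariate list omits both factors while keeping one that the exclusions leave nearly uninformative.

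The between-arm comparison is not biased by this, and type I error stays near 5%. Unadjusted chance imbalance is worth roughly 0.04 to 0.14 grade under the assumed correlations, so it would not by itself overturn an effect near 0.78. Dilution matters only if a large share recovers in both arms: power is 95%, 68% and 49% at 25%, 50% and 60%, given a gap of 0.78, SD 0.545 and 24 evaluable per arm.

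One conditional route to bias remains. Under Dropout and suspension criteria, patients with less than 3 months of intervention count as not having completed outcome evaluation. If recovered patients stop at different rates by arm, missingness becomes informative, and an imputation model without recency and severity could not allow for their part in it. The documents do not show that this will happen.

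The limit on attribution does not depend on any of these figures.

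**What to change.** 1. At baseline, take the date of discharge (or diagnosis) and the acute severity class from the discharge record. Both are settled before randomisation.
2. In Analysis of primary outcome, replace history of cardiopulmonary disease with days since discharge (continuous) and acute severity. Use them with baseline mMRC in the adjusted primary analysis and in the chained-equations imputation model. State a model that can carry covariates, since the t-test and ANOVAs named there do not as described.
3. Reconcile the post-COVID-19 syndrome wording in the Abstract with the population admitted: state the conclusion for convalescent patients after discharge, unless the sponsor itself defines an entry interval. Whether to set such an interval, and which, is an eligibility decision for the sponsor that the May to December 2022 calendar may not allow; the fix does not depend on it.

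Cost: two or three baseline items, one net additional model term beyond baseline mMRC (more if severity has several unordered classes), and a narrower stated conclusion. Enrolment and treatment are unaffected.

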### Exclusion criteria

Any involvement in the following condition will be removed: (1) patients with complications of underlying noncommunicable diseases such as chronic obstructive pulmonary disease, coronary heart disease, dementia, chronic kidney disease, immunosuppression, and cancer; (2) patients with mental illness; (3) patients with cognitive dysfunction until unable to understand the whole trial process; (4) patients with severe bone or joint diseases that affect movement (e.g., spinal arthritis, severe osteoporosis, and periarthritis); (5) patients with pregnancy or lactating; (6) cigarettes smokers; (7) patients who participate in other form of exercise programs during trial.

### Dropout and suspension criteria

Under the protection of the Declaration of Helsinki [26], patients are allowed to withdraw themselves from the clinical research at any time. In addition, if the intervention time is below 3 months, subjects will be considered as not completed the outcome evaluation.

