### Interventions

In this study, a total of 60 recruited participants will be randomized into the BT group or the KQG group. Both exercises last 15 min per time and each program will be performed twice a day at 10 am and 4 pm [27]. Thus, a total of 30 min will be needed every day [28]. A 3-week treatment comprised one course. The intervention will last for 3 months in both our groups and then both will be followed up for a further 3 months.

The exercise of both groups will be demonstrated and monitored by the therapists on the first day until the patient is able to perform the exercises proficiently. Text instruction and video demonstration of the exercises will be provided to patients for subsequent practice. After patients are familiar with the basic movements, they can increase the intensity and focus on the breathing under the guidance of the therapists. Therapists performing TCMRE will be required to have a minimum of 10 years’ clinical experience in Qigong therapy, and they must have undergone meticulous clinical trial training before conducting trials until passing an exam to perform the intervention. In addition, participants in both groups will be allowed to exercise normally under intervention conditions.

The exercise of both groups will be demonstrated and monitored by the therapists on the first day until the patient is able to perform the exercises proficiently. Paper and video versions of the exercises will be provided to patients for subsequent practice. After patients are familiar with the basic exercise, they can increase the intensity and focus on the breathing under the guidance of the therapist. Therapists performing TCMRE will be required to have a minimum of 10 years clinical experience in Qigong therapy. And they must have undergone meticulous clinical trial training before conducting trials until passing an exam to perform the intervention. In addition, participants in both groups will be allowed to exercise normally under intervention conditions.

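### Under 3 months of exercise counts as not evaluated, and intention-to-treat appears only as a sensitivity analysis, so the main comparison may be restricted to completers

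*Protocol article*

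**What the plan says.** All references are to the protocol article.

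- **Dropout and suspension criteria:** after allowing withdrawal at any time, the section adds that "if the intervention time is below 3 months, subjects will be considered as not completed the outcome evaluation".
- **Analysis of primary outcome, intention-to-treat:** the term is used only here: "We will conduct sensitivity analyses for missing data (intention-to-treat analysis) and for adjustment of covariates of physical activity (adjusted intention-to-treat analysis").
- **Analysis of primary outcome, missing data:** "A sensitivity analysis using multiple imputation techniques (imputation using chained equations) will be included to assess the effect of missing data on the primary outcome". Missing data are put at 20%, and reasons and patterns are to be examined.
- **Analysis of primary outcome, main comparison:** an unpaired t-test, with one-way and repeated-measures ANOVA for multiple comparisons, on change in mMRC from baseline to follow-up. No analysis set is attached to it. A comparison of participants with high-fidelity treatment is listed separately.
- **Other exercise:** inclusion criterion 6 asks for a promise to do none. The Exclusion criteria open with "Any involvement in the following condition will be removed" and list, as item 7, "patients who participate in other form of exercise programs during trial". The Interventions section says, twice, that "participants in both groups will be allowed to exercise normally under intervention conditions".

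**The concern.** Stopping the exercise and having no outcome are different events. A participant who stops at week 8 can still be asked the mMRC question at 3 months and at follow-up. The dropout rule merges the two, so an obtainable outcome is classed as incomplete because of something that happened after randomisation.

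If those participants then fall out of the main comparison, it is no longer protected by randomisation. Participants and clinicians know the allocation (Blinding; Study limitations). The programmes differ physically: breathing control while seated plus pacing of effortful activities in one arm, and seven sets of mainly standing movements with twisting, kicking and heel-stamping in the other. Who stops, and why, could therefore differ by arm and be related to dyspnoea, which is the primary outcome.

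The planned sensitivity analyses do not fully repair this. Imputation would fill in values for early stoppers largely from participants who kept exercising, where an actual score could have been collected.

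**Working it through.** **1. What the text fixes and what it leaves open**

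| Question | Answer in the article |
|---|---|
| Status of under 3 months of intervention | Outcome evaluation not completed |
| Role of intention-to-treat | Sensitivity analysis, plain and adjusted |
| Role of multiple imputation | Sensitivity analysis |
| Set for the main t-test or RM ANOVA | Not named |
| Are early stoppers still followed and analysed? | Not stated |

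If intention-to-treat and imputation are the departures from the main analysis, and early stoppers are unevaluated by rule, what remains for the main analysis is most naturally the completers. This is an inference from the first three rows; no sentence says it.

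**2. How large a bias could be**

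The article gives no figure to reproduce on this point: no stopping rates by arm and no outcome gap between stoppers and completers. The following is an illustration.

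Inputs from the article:
- SDs 0.55 and 0.54 (Sample size calculation), pooled SD = √((0.55² + 0.54²)/2) = 0.545.
- 30 per arm (Fig. 1) less 20% loss = 24 per arm.
- Two-sided α = 0.05.

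Assumptions: no true effect; a fraction f of an arm stops; stoppers score g grades worse than completers in both arms.

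Formula: overall mean = completer mean + f·g, so completer mean = overall mean − f·g. With equal overall means, the completers' difference is

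bias = g × (f₁ − f₂).

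Standard error = 0.545 × √(2/24) = 0.157. The rejection rate comes from the noncentral t with 46 degrees of freedom and noncentrality bias/0.157.

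| f₁ − f₂ | g | Bias (grades) | Noncentrality | Type I error |
|---|---|---|---|---|
| 0 | any | 0 | 0 | 5% |
| 0.10 | 0.55 | 0.055 | 0.35 | 6.4% |
| 0.15 | 0.55 | 0.0825 | 0.52 | 8.1% |
| 0.10 | 1.0 | 0.10 | 0.64 | 9.5% |
| 0.15 | 1.0 | 0.15 | 0.95 | 15.4% |

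A difference in loss implies unequal numbers. With 12.5% and 27.5% loss (average 20%), 26.25 and 21.75 remain per arm, SE = 0.545 × √(1/26.25 + 1/21.75) = 0.158, and the last row becomes 15.3%. Using 24 per arm is therefore harmless.

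**3. Is lost power the issue?**

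No. At the article's assumed difference of 1.52 − 0.74 = 0.78, power with 24 per arm is about 99.9%. What exclusions threaten is the validity of the estimate.

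**The case against.** **The primary set is never named.** Analysis sets are commonly left to an SAP, which is not shown, and listing the high-fidelity comparison separately hints that the main comparison is not limited to adherent participants. This stands: a reader may infer that the main result is a completers' comparison, but the article supports only that it may be. An SAP could define the set otherwise, but it would have to override the wording of two sections.

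**Missing data are addressed.** Imputation, reasons for missingness and patterns are all planned. This stands in part: selective loss will be examined, but only at sensitivity level, and after collectable outcomes have been classed as incomplete.

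**The illustration is assumed.** This stands. A 1-grade gap is 1/0.545 = 1.8 SD and exceeds the planned difference of 0.78. The milder case barely exceeds 5%. A bias of 0.055 to 0.15 is 7% to 19% of 0.78. The SD is of scores, whereas the endpoint is a change.

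Three stronger readings are tempting but not supported:

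- *Participants who take up other exercise are dropped from the analysis.* Item 7 sits in an eligibility list applied at screening, and its introductory verb also covers pregnancy and smoking, so it may just mean excluded. The planned adjustment for physical activity suggests that such participants stay in at least one analysis. Removal from analysis is one reading only.
- *The worst outcomes are discarded because participants who deteriorate are stopped.* The Safety evaluation section deals with stopping and medical care and says nothing about discarding data.
- *A full course fails the rule because "this trial will include a 12-week treatment period", that is 84 days, against about 91 in 3 months.* The article uses the two terms interchangeably, and the literal reading would leave nobody evaluable.

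**Conclusion.** The point holds as a defect in what the article states. Following it literally, obtainable outcomes of early stoppers count as incomplete, while intention-to-treat and imputation are secondary checks on a main comparison whose population is undefined. The primary estimate of an open-label superiority trial may therefore rest on completers.

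The resulting bias has unknown direction and size. Under the stated assumptions it ranges from zero, when loss is equal and non-informative, through 0.055 grade (about 6% type I error) to 0.15 grade (about 15%). Nothing in the article makes any of these the expected case.

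Separately, inclusion criterion 6, exclusion criterion 7 and the Interventions section give conflicting statements on other exercise during the trial. Until they are reconciled, whether a participant is removed is open to judgement made with knowledge of the arm.

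**What to change.** 1. **Analysis of primary outcome:** name intention-to-treat as the primary analysis, meaning all randomised participants in their assigned group, with multiple imputation for outcomes that are truly missing.
2. **Dropout and suspension criteria:** let under 3 months of intervention define non-adherence only, and state that mMRC is still collected at every visit from those who stop, unless they withdraw from follow-up.
3. **Supplementary analyses:** keep the completer and high-fidelity comparisons, labelled as such.
4. **Other exercise:** reconcile inclusion criterion 6, exclusion criterion 7 and the Interventions section. Whichever rule the trial team adopts, state that participants who do other exercise after randomisation stay in the primary analysis.

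**Cost:** changes of wording, and some follow-up contact with participants who stop; the Adherence section already provides weekly calls. The effect estimate may be diluted by non-adherence. At the article's assumed difference there is ample power to absorb this, though a smaller true effect would leave less room. Scores not collected at the time cannot be recovered later, so items 1 and 2 should be settled before outcome visits take place.
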